
### Criteria for discontinuing or modifying allocated interventions

According to the criteria for discontinuing allocated interventions, the intervention will be discontinued when the participants ask to withdraw or when their health conditions worsen. In addition, the parts of the intervention that patients think are too intense to adhere to or to be unreasonable will be revised. During the intervention, we will also carefully record any suggestions given by patients and make adjustments after complete discussion.

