## Abstract

**Background:**

Adverse reactions are prone to occur in the early stage of chemotherapy and can negatively affect the dietary intake and nutritional status of breast cancer (BC) patients. Consequently, they need to participate in health self-management and lifestyle promotion programs. Early multidisciplinary interventions aim to enhance dietary management behavior and quality of life in chemotherapy-treated BC patients.

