There are few existing studies about dietary management interventions for cancer patients during chemotherapy, and the available studies lack specificity. First, regarding the intervention population, most studies [8–10] have focused on BC survivors who have completed all adjuvant therapy. However, many females report the most severe side effects during chemotherapy. They do not know how to cope with these side effects and receive little support during treatment [11–13]. Thus, early dietary intervention is needed. Regarding intervention content, most cancer patients are thought to be provided with professional nutritional supplements [14, 15]. The nutritional status of most cancer patients does not reach severe pathological malnutrition. Instead, they can feed themselves orally and desire increased knowledge about nutrition and dietary precautions. Implementing DMB interventions is highly beneficial. These interventions can stimulate patients’ sense of autonomy, cultivate their nutritional management ability, provide a basis for the implementation of home-based rehabilitation plans after chemotherapy, and ultimately improve their life expectancy and quality of life [5].

Additionally, diet and nutrition promotion are usually framed as the work of oncologists and dietitians. Nevertheless, diet is an integral part of one’s lifestyle and a health management behavior that includes physiological, psychological, environmental, societal, and cultural elements [16, 17]. In China, cancer patients also desire advice on food therapy or integrative medicine from traditional Chinese medicine (TCM) practitioners [18, 19]. A multidisciplinary team (MDT) comprising oncologists, dietitians, clinical nurses, TCM practitioners, and psychologists may be suitable for providing diet management interventions.

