Intervention session 1 (topic: adverse reaction management): After the participants receive chemotherapy during admission and 1 day before hospital discharge, the MDT members will introduce themselves and the describe intervention process face-to-face, and patients will become familiar with each other. This session will include group interventions, group discussions and lectures: (1) patients will share their experiences with chemotherapy and diet; the group will discuss their own disease and chemotherapy experiences and diet change trajectory; (2) a nurse will show a professional video from the China Central Television (CCTV) “Health Road” program about BC, chemotherapy and diet; (3) oncologists, nurses, and dietitians will introduce the trend of common adverse reactions and the corresponding dietary self-management tips during different chemotherapy periods, including early, middle, and late-term chemotherapy or chemotherapy during admission or the interval period; and (4) oncologists will clarify the boundaries between dietary self-management and medication management when adverse reactions occur.Intervention session 2 (topic: dietary information and habit regulation): A combination of online group and individual intervention sessions will be conducted during the first week of the home-based interval chemotherapy period after session 1, which will include the following: (1) oncologists and dietitians will hold an online group Tencent conference to introduce authoritative sources of dietary information for cancer patients, such as WeChat public accounts, short videos, guidelines, and distributed information in the form of electronic materials; (2) dietitians and TCM practitioners will focus on correct dietary habits and misunderstandings for individuals with different demographic characteristics during telephone calls or WeChat messaging, including discussing the relationship between dietary intake and hormone levels for hormone receptor-positive patients, providing nutrition and weight management clinics and food therapy for patients with higher family income or abnormal weight; and (3) dietitians will demonstrate methods of dietary intake self-assessment by online video presentations, using simple and intuitive representations such as “a handful, a fist, 1 g or 2 g of quantitative salt spoons”.Intervention session 3 (topic: self-care self-efficacy training): The online group session during the second week of interval chemotherapy after session 1 will include the following: (1) nurses will guide patients to disclose their concerns about participating in their diet self-management; (2) the psychologist will lead “evidence check” and “advocate” sessions: patients will be asked to write evidence for and against their participation in dietary self-management on two post-it notes and then play the advocate, attacking the evidence against participation; and (3) nurses will provide diet option comparison cards to show patients the pros and cons of different dietary habits and encourage all patients to choose and share the reasons.Intervention session 4 (topic: treatment self-regulation training): Online group and individual sessions will be conducted during the third week of interval chemotherapy after session 1, which will include the following: (1) Through WeChat, the psychologist will send patients an assessment questionnaire linked to treatment self-regulation. According to the results, the patients will be divided into four groups: the autonomous motivation, introjected regulation, external regulation, and amotivation groups [31]. Then, the psychologist will explain definitions, content, and performance to the same online group Tencent conference; (2) the psychologist will explain the relationship between mood and diet and then use “identifying automatic thoughts” and “testing hypotheses” to determine the cognitive reasons for the lack of motivation among patients in the amotivation group in the process of participating in diet self-management and demonstrate stress relief techniques, such as deep breathing and listening to soothing music; and (3) nurses will invite patients in the autonomous motivation and introjected regulation groups to share their diet self-management experiences and the goals achieved.Intervention session 5 (topic: dietary supplement and TCM use): The next admission chemotherapy period after the session, which will include a face-to-face group lecture and discussion one day before hospital discharge, will include the following steps: (1) dietitians and TCM practitioners will use videos, charts, and paper materials to explain the concept, indications, and types of dietary nutritional supplements and replacement therapy (which can be divided into two categories: edible nutritional supplements as well as complementary and alternative therapies, such as moxibustion, massage, and aromatherapy); (2) through clinical practice and scenario simulations, using pictures or natural objects, oncologists and dietitians will guide patients in analyzing and choosing dietary supplements and replacement therapies according to their conditions; and (3) TCM practitioners will describe the content of food therapy that Chinese patients are interested in, popularize scientific knowledge and correct misunderstandings.Intervention session 6 (topic: social support seeking): Online group and individual sessions will be performed during the first week of home-based interval chemotherapy after session 5, which will include the following: (1) warm small things to share and express gratitude: nurses will encourage patients to write down the names of people who prepare their meals and living arrangements during chemotherapy through an online group Tencent conference and prepare a sentence, video or gift for them. (2) The psychologist will provide targeted dietary management tips related to emotion and psychology depending on the working status of patients via WeChat or telephone. For employed females, dietary advice will be provided to their families or colleagues before they return to work. Nonemployed individuals will be encouraged to share their thoughts and preferences regarding their diet with friends or neighbors who would like to help take care of them. (3) Nurses will encourage patients to share how others can help improve their diet during chemotherapy and how they seek help.Intervention session 7 (topic: weight management): Online group and individual sessions will be provided during the second week of the interval chemotherapy period after session 5, which includes (1) oncologists informing patients that being overweight is a risk factor and showing patients how to correctly measure their body weight via an online video, calculate their body mass index (BMI) and determine their BMI classification. (2) Dietitians will introduce the criteria and ranges of daily caloric intake for patients with different BMI classification via WeChat or telephone. For example, overweight and obese patients will be taught to read ingredient lists and recipes. Patients with a BMI below the normal range will be taught to choose foods rich in high-quality fat (such as omega 3 fatty acids and monounsaturated fatty acids) and protein [29, 30]. Repeated operations and repetitions will be used to test the effect. (3) Nurses will show patients and their caregivers how to exercise moderately and record daily calories using apps or memos.Intervention session 8 (topic: outcome expectation education): An online group session during the third week of interval chemotherapy after session 5 will include the following: (1) the psychologist will introduce the concept, content, necessity, classification and function of the outcome expectation related to dietary self-management to patients by an online group Tencent conference; (2) Nurses will encourage patients to write down their expectations for diet self-management on post-it notes and classify them into immediate or future goals; (3) The psychologist will use the “five-column chart” of alternative thinking to ask patients to share their views on the outcome expectations and determine the negative cognition of achieving the goal; (4) Through scenario and case studies, the psychologist will lead patients to analyze their own cognition on two outcome expectations of what points may be right or wrong, encourage them to create new goals and teach them how to stick to long-term dietary self-management monitoring; and (5) MDT members will summarize and share the gains and suggestions of this intervention with patients.

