### Statistical analysis

We will use IBM SPSS Statistics 21.0 software to analyze the statistical data. Descriptive statistics, such as the number of patients with different ages, education levels, cancer stages and types of chemotherapy, as well as the percentage of patients in different groups relative to the total number of patients, will be calculated for different groups of demographic and clinical information. The mean and standard deviation will be used to compare the DMBQ total and dimensions scores, the SUPPH and FACT-B scores, and BMI. To compare the baseline balance between the two groups, two independent sample *t* tests, chi-square tests or Mann‒Whitney U tests, will be used, depending on whether the data distribution satisfies homogeneity of variance. The Shapiro‒Wilk test will be used to verify whether the scores of the two groups at different time points follow a normal distribution. If the data are balanced, repeated ANOVA will be adopted. Otherwise, we will use a generalized estimating equation (GEE) to analyze the intervention’s time, group, and interaction effects [36]. For all the above tests, *P* < 0.05 will indicate a statistically significant difference, the α level will be 0.05, and the tests will be two-sided. We will use intention-to-treat (ITT) analysis to minimize bias for sensitivity analysis [37]. The results of the last measurement of the patients who drop out of the study will be taken as the effect, which assumes that they complete the intervention, and the analysis will be reconducted with the GEE. Furthermore, missing data will be imputed with the mean values of the characteristics or with the help of multiple imputation methods if they are random and unrelated to the research elements.

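### Stopping sessions for undefined worsening, with follow-up timed from session eight and ITT kept for sensitivity, leaves patients stopped early without a defined assessment or a place in the main analysis

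*Protocol article*

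**What the plan says.** Four parts of the protocol article bear on this.

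- **Criteria for discontinuing or modifying allocated interventions.** The rule is that "the intervention will be discontinued when the participants ask to withdraw or when their health conditions worsen". It gives no degree or cause of worsening, and it does not mention follow-up or analysis.
- **Implementation, session 1, and the background.** The session is headed "Intervention session 1 (topic: adverse reaction management"). In it, staff "introduce the trend of common adverse reactions and the corresponding dietary self-management tips during different chemotherapy periods", and "oncologists will clarify the boundaries between dietary self-management and medication management when adverse reactions occur". The abstract says that "Adverse reactions are prone to occur in the early stage of chemotherapy and can negatively affect the dietary intake and nutritional status" of these patients, and the Background adds that "many females report the most severe side effects during chemotherapy".
- **Study design.** T1 is taken once session eight has finished. T2, T3, T4 and T5 fall 30, 90, 180 and 360 days after the T1 date. The control group uses the same time points.
- **Statistical analysis.** The main analysis is repeated-measures ANOVA if the data are balanced, otherwise GEE. Intention-to-treat is named for sensitivity analysis. There, "The results of the last measurement of the patients who drop out of the study will be taken as the effect", on the stated assumption that these patients completed the intervention, and the GEE is rerun.

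**The concern.** Read literally, the stopping rule can be set off by events that the article expects in this population and gives as a reason for intervening early. In practice it can act on one arm only, because usual care has no scheduled programme to stop.

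That alone would cause no bias. The difficulty comes from combining it with the other two provisions. A patient whose sessions stop before the eighth never reaches the event that defines T1, and so has no dates for T2 to T5. The main analysis is not tied to the randomised population, and the analysis that is so tied uses carried-forward values. Following the text as written can therefore lose or misrepresent intervention patients who become unwell, while controls who become equally unwell are still assessed. At stake is the between-group comparison on the self-reported DMBQ (primary outcome) and FACT-B.

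**Working it through.** The plan gives no figure for this point, so there is nothing to reproduce. The check is a trace through the text, followed by an illustration on assumed inputs.

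**Trace.** Take an intervention patient whose sessions stop for worsening after, say, session 3.

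1. T1 is defined by the end of session eight, which does not occur. T2-T5 are counted from T1 and are also undefined.
2. No assessment is scheduled between T0 and T1. If nothing is collected after stopping, her last measurement is T0, taken before the worsening.
3. In the main analysis she has no post-baseline value, and the article does not say whether she is included.
4. In the sensitivity analysis her T0 value stands in for T1-T5, as if she had completed the programme.
5. A control who worsens to the same degree has no programme to stop, so nothing in this rule interrupts her assessments. If assessed, she contributes her actual scores.

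**Illustration A: stopped patients left out.** Assumed: the lowest fraction p of the intervention arm on a normally distributed health measure is excluded, no controls are excluded, and health correlates r with the outcome. With φ the standard normal density and z_p its p-quantile, the shift in the arm mean with no true effect is r × φ(z_p)/(1 − p).

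- p = 0.10 (44 × 0.10 = about 4 patients): 0.1755/0.90 = 0.195. Times 0.3 and 0.5: 0.06 and 0.10 SD.
- p = 0.25 (44 × 0.25 = 11 patients): 0.3178/0.75 = 0.424. Times 0.3 and 0.5: 0.13 and 0.21 SD.
- p = 0.20, equal to the planned loss from all causes: 0.2800/0.80 = 0.350. Times 0.3 and 0.5: 0.105 and 0.175 SD.

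If the planned effect size of 0.25 is Cohen's f for two groups, it equals d = 2 × 0.25 = 0.5. The range is then 0.0585/0.5 = 12% to 0.212/0.5 = 42% of it. The article says only ANOVA, so that conversion is an assumption too.

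**Illustration B: a simpler form.** If a share p of the arm scores d SD below the rest of it and is left out, the arm mean rises by p × d. Type I error is for a two-sided z test of 44 against 44(1 − p), with SE = √(1/44 + 1/[44(1 − p)]).

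- p = 0.05, d = 0.25: 0.0125 SD (about 0.01), type I error 5.0%.
- p = 0.10, d = 0.5: 0.05 SD, type I error 5.6%.
- p = 0.20, d = 1: 0.20 SD, SE = √(1/44 + 1/35.2) = 0.226, type I error 14.3%.

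**Carry-forward.** If a share p is kept but given a baseline value c SD above the score it would have had, the arm mean rises by p × c. The sign follows the time course: it favours the intervention if scores fall during chemotherapy and works against it if they rise.

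**Followed and analysed as randomised.** No one is excluded or substituted, so the selection bias is zero. Stopping sessions then only dilutes the effect.

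**The case against.** The strongest reply is that the rule removes nobody from anything. It opens with "According to the criteria for discontinuing allocated interventions" and stops the intervention only. A reader might infer that it takes the sickest patients out of the intervention arm, but the article does not say so, and that they would be the sickest is itself a guess. Worsening may be meant as deterioration that prevents participation, in line with the eligibility requirement of a physical and mental state that allows the programme to proceed. This stands, and it is why the bias is stated conditionally.

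A reader might also infer that harms could no longer be compared between arms. The article does not support this. Data management and monitoring provides regular adverse-event follow-up by telephone or home visit, without limiting it by arm or ending it when sessions stop, and a monitoring board reviews adverse events.

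Other replies stand in part. Session 1 is one of eight and is educational, so the overlap with expected reactions is one of wording rather than a proven contradiction. Controls do receive lectures, manuals and remote help as needed, although none of this is a programme that the rule could realistically stop. The sizes rest on assumed inputs, and 25% stopped for worsening in one arm would exceed the whole planned loss of 20%. Controls who become ill may drop out too.

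Finally, thresholds and documentation may sit in a full protocol that is not shown, so their absence is not counted here. What the article does fix is the timing of T1-T5 and the role of intention-to-treat. Sessions are weekly, so one could read T1 as the planned week of session eight, but the article defines T1 by completion of that session.

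**Conclusion.** The concern holds in a limited form. The stopping trigger is undefined, overlaps with the reactions addressed in session 1, and can in practice stop only the eight-session programme. Together with a T1 tied to completing session eight and intention-to-treat reserved for a last-value sensitivity analysis, it leaves patients stopped early with no defined post-baseline assessment and no stated place in the main analysis.

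The bias is possible, not demonstrated. It is 0.06-0.21 SD if the worst 10-25% of one arm are excluded and health correlates 0.3-0.5 with the outcome, all of these being assumed values. It is zero if those patients are followed and analysed as randomised. Under carry-forward its direction depends on how scores move during chemotherapy. The correction is cheap and should be made, but the point does not undermine the trial's safety follow-up.

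**What to change.** Reconcile the sections on study design, implementation (session 1), discontinuation criteria and statistical analysis:

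- The sponsor should clarify how worsening in the stopping rule relates to expected chemotherapy reactions. No clinical rule is proposed here.
- State that stopping sessions is not withdrawal from the study, and record the reason for each stop.
- Schedule T1-T5 in both arms by calendar time, from randomisation or from the planned session dates, whether or not session eight takes place.
- Keep collecting outcomes unless consent is withdrawn.
- Analyse these patients in their randomised group in the main analysis, not only in a sensitivity analysis.

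The cost is protocol wording and a few more electronic questionnaires. The downside is some extra burden for unwell patients, who may decline.

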### Intervention fidelity

A nurse not involved in this trial will evaluate the fidelity of the intervention using the Modified Fidelity Checklist (MFC) [32]. This checklist comprises the adherence (18 items) and competence subscales (14 items) and a cover page about the intervention setting, times, number of participants in each group, etc. For the former subscale, all items are coded “yes” or “no,” with comments in the subsequent column. The first three items and the last item belong to the knowledge survey pretest and posttest, respectively, to determine the knowledge benefits related to the multidisciplinary early diet management intervention. The remaining 14 items reflect the content of this intervention. The latter subscale assesses whether the intervention promotes increased effort to facilitate patients’ efforts to achieve their intervention goals. Items are coded as “1 = skill rarely or never demonstrated, 2 = skill sometimes/occasionally demonstrated, and 3 = skill consistently demonstrated”, with additional qualitative feedback on the skill for an item.

### Control group: usual care

The patients assigned to the control group will receive standard admission health education from the department. The main contents include the following: After the BC patients are admitted to the hospital, the doctor will ask about the patient’s condition and provide basic BC disease information. Nurses will distribute health education manuals, such as adverse reactions and coping methods related to chemotherapy. In addition, oncologists and nurses will provide clinical group lectures to explain the relationship between chemotherapy and diet, dietary information and strategies (mostly from the Dietary Guidelines for Chinese Residents, the World or American Guide, etc.), the necessity of weight management, etc. Health professionals will use face-to-face communication, question answering, demonstrations, and other methods during admission for chemotherapy to solve dietary problems. Patients who need food therapy will be evaluated by doctors and provided with relevant knowledge, precautions, indications and contraindications. During the home-based chemotherapy interval, telephone calls, WeChat messaging, online conferences, emails, and other forms of assistance will be provided to BC patients as needed. As is usual practice, no specific or individual recommendations will be provided.

